### Outcome measures

Exercise tests will be analyzed by a pulmonologist with experience in cardiopulmonary exercise test interpretation. This assessor will be masked to exercise position.

### Primary outcome measure

The primary outcome will be the difference in stopping time between the upright and supine exercise positions. We will exclude participants who stopped the exercise test due to either life-threatening arrhythmia or a drop in systolic blood pressure from the primary outcome analysis.

### Secondary outcome measures

Secondary outcomes will include differences in the following variables at isotime: oxygen uptake (VO_2_), minute ventilation (VE), work rate, heart rate (HR), arterial oxygen saturation (SpO_2_), dyspnea, leg fatigue, change in inspiratory capacity, and carbon dioxide production (VCO_2_). We will also compare the reason for stopping exercise (leg fatigue, dyspnea, other) and maximum minute ventilation (*VE*_max_). In patients who reach anaerobic threshold (AT) in both positions, we will compare time to reach AT, and VO_2_, VE/VCO_2_, and cardiac output at AT in each position. Relationships between key variables will be compared graphically, including VCO_2_ over VO_2_, HR over VO_2_,VE over VCO_2_, end-tidal CO_2_ (PetCO_2_) over time, saturation over time, VE over time, and VO_2_/HR (“oxygen pulse”) over time and HR over time. We will also conduct exploratory subgroup analyses, investigating the effects of baseline values such as PaO_2_ and degree of orthodeoxia on exercise variables.

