### Exercise protocol

Each participant will perform a constant work rate exercise test (CWRET). The constant work rate will be individualized for each participant and set at 70–85% of their estimated peak work rate [25], targeting an estimated test duration of 180–480 s (to increase the chances that exercise limitation is due to the physiologic effects of exercise rather than physical discomfort or boredom [26]). Peak work rate will be estimated from a previous room air 6-min walk test (6MWT) performed within the last 6 months (peak work rate = 0.168 × 6MWD (m) − 4.085) [27].

The CWRET will include a warmup period consisting of 1 min of rest during which participants will be in set position with their feet planted on the pedals, without pedaling. This will be followed by an immediate ramp-up to the predetermined target constant work rate [25, 26]. Patients will be instructed to pedal at a rate between 50 and 60 revolutions per minute (rpm) and will be provided with constant feedback on pedaling frequency through a biofeedback display. We will also provide standardized verbal encouragement throughout [28], relating when they are above or below the target pedaling frequency, congratulating them when they are within the target frequency, and encouraging them to continue pedaling for as long as they feel able to. For each participant, exercise in each position will be standardized with respect to the proper seat adjustment relative to leg length and pedaling cadence. Upright cycle ergometry will be performed on the Corival Ergometer Bicycle (LODE B.V. Medical Technology Groningen, the Netherlands) at an angle of 90°. The supine cycle will be performed on the Stress EchoBed® (Medical Positioning Inc., USA) at an angle of 0°. For both tests, all measurements will take place through a pitot tube spirometer. Volume and flow calibrations (pitot tube spirometer) and gas calibration (Ergo Card Analyzer, Medisoft, USA) will be performed within 1 h of the exercise test, and Bio calibration will be performed on the pitot tube spirometer every 3 months.

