Inspiratory capacity will be measured before and after exercise. Before, after, and throughout exercise, we will measure the following: oxygen uptake (VO_2_) and carbon dioxide production (VCO_2_) (measured breath-by-breath, averaged over 30-s epochs), oxygen saturation and heart rate (continuously, by pulse oximetry and 12-lead electrocardiography, respectively), blood pressure (every 2 min, by manual sphygmomanometry), and subjective dyspnea and leg fatigue (every 1 min, by modified Borg scale) [29]. Participants will continue exercising until they reach one of the following stopping criteria: 1) the point at which, after standardized encouragement, the participant is unable to continue because of symptoms (i.e., participant does not wish to continue or is unable to maintain a minimum peddling frequency of 40 rpm for ≥ 10 s) [defined as the “tolerable limit” (tLIM)]; 2) desaturation below a set point for ≥ 30 s; 3) a drop in systolic blood pressure by ≥ 10 mmHg from baseline; or 4) the appearance of life-threatening arrhythmias (such as significant ventricular arrhythmias or high-grade heart block). The low saturation set point will be chosen individually for each participant, as the lower of 80% [26], or the nadir desaturation seen on baseline room air 6MWT. Stopping time will be defined as the duration of pedaling during the constant workload exercise test before a stopping criterion was met. During the test, the stopping time and criterion will be determined by agreement between the PI and the experienced technician conducting the test. Upon agreement, the time and criterion will be designated within the CPET software and independently recorded on a data collection sheet by a research assistant (the assistant will also use a stopwatch during the test to independently record timing, ensuring that stopping time is measured in duplicate to account for any system failures or errors). The dropout criteria for this study include unwillingness/inability to return for the second test or presence of one of the arrhythmic or hemodynamic-related stopping criteria on the first of the protocolized exercise tests (a safety-related dropout).

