### Study population and design

We chose to include patients with at least moderate HPS (PaO_2_ < 80 mmHg), in order to ensure that the degree of observed orthodeoxia is both clinically and physiologically significant. Tissue oxygen delivery (DO_2_), which is the physiologic substrate for the hypothesized position-related changes in exercise capacity that we seek to demonstrate, is dependent on oxygen saturation, which is in turn correlated with PaO_2_ through the sigmoidal oxyhemoglobin dissociation curve. Given the flat shape of this curve at higher PaO_2_ levels, changes in PaO_2_ of just over 4 mmHg (the definition of orthodeoxia) would not result in any significant changes in oxygen saturation in patients with a baseline PaO2 ≥ 80 mmHg.

Our use of a CWRET protocol is novel in this population, as prior studies of exercise testing in HPS (Table 1) have almost exclusively employed incremental exercise protocols [7–9, 12]. Given the severe baseline disease in our expected patient population (Table 3), with a predicted mean PaO_2_ drop of 20 mmHg at peak exercise [7], we believe that an incremental exercise protocol would result in profound desaturation requiring cessation for safety reasons, with a high resulting likelihood of a submaximal test. Accordingly, the main variable of interest in an incremental exercise protocol, VO_2peak_, would not likely be achieved in most participants. To address this, we chose a high-intensity CWRET, which has been widely used to assess the changes in exercise tolerance following interventions in other chronic hypoxemic lung diseases [26].

The constant work rate in a CWRET is typically set at 70–85% of the peak work rate measured on incremental exercise testing (IET) [26]. Given that an IET was not feasible in our population, we instead adopted a validated prediction equation for estimating peak work rate based on 6-min walk distance (6MWD) in patients with COPD [27, 41]. Given that peak work rate is affected by ventilatory impairment and dynamic hyperinflation in COPD, neither of which appears to play a role in HPS, this represents a vulnerability in our testing protocol.

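### The secondary outcomes at the anaerobic threshold cannot be located by the trial's only test, which goes straight from rest to a constant load

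*Protocol article*

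**What the plan says.** Secondary outcome measures in the protocol article plans four comparisons tied to the anaerobic threshold (AT). The first is stated as: "In patients who reach anaerobic threshold (AT) in both positions, we will compare time to reach AT". The other three, in the same sentence, are VO2, VE/VCO2 and cardiac output at AT. They are limited to patients judged to reach AT in both tests.

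Exercise protocol describes one kind of test, done once in each position. The load is "set at 70–85% of their estimated peak work rate". It is preceded by one minute sitting or lying with the feet on the pedals and no pedalling. Then: "This will be followed by an immediate ramp-up to the predetermined target constant work rate". The load is held until a stopping criterion is met. VO2 and VCO2 are "measured breath-by-breath, averaged over 30-s epochs". The listed measurements include no blood lactate.

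The Discussion (Study population and design) explains why peak work rate is predicted from walking distance: "Given that an IET was not feasible in our population". No other test in the trial could therefore supply an AT.

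**The concern.** Read from gas exchange, AT is the metabolic rate at which VCO2 or ventilation breaks away from VO2 as work rate climbs. The trial has no phase in which work rate climbs, so the endpoint and the test do not match. The article's own AT finding in this disease (Table 1, earlier onset) comes from incremental cycle ergometry.

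What is at stake is interpretation. Study rationale and purpose reports that supine exercise lowers the anaerobic threshold in healthy people. A reader who expects a positional effect could take a difference in the apparent AT as physiology when the test had not located a threshold in either position.

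**Working it through.** The article gives no figure for the AT outcomes, so there is none to reproduce. The check has three steps.

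**1. Does any planned measurement locate AT?**
- Graded load: none. Exercise protocol goes from rest to the full target load.
- Incremental test: none, by the Discussion's own statement.
- Lactate: not among the listed measurements.
- For scale, the orthodeoxia group's mean walking distance in Table 4 is 441.8 m. Predicted peak is 0.168 × 441.8 − 4.085 = 70.1 W, so the load is 0.70 × 70.1 = 49 W to 0.85 × 70.1 = 60 W from the start of pedalling.

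Two cases remain. With a load below AT, AT is not reached. With a load above AT, VO2 passes that level on its way to the plateau. Neither case locates the threshold.

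**2. When would VO2 pass the AT level?**

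From the document: load 70–85%. Assumed, not in the document: mono-exponential VO2 rise, time constant τ of 30–70 s, starting VO2 25% of peak, AT at 50–60% of peak, and a VO2 plateau P at the same percentage as the load.

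Formula: t = τ × ln[(P − 0.25) / (P − AT)]

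| P | AT | ln term | τ = 30 s | τ = 70 s |
|---|---|---|---|---|
| 0.85 | 0.50 | ln(0.60/0.35) = 0.539 | 16 s | 38 s |
| 0.85 | 0.60 | ln(0.60/0.25) = 0.875 | 26 s | 61 s |
| 0.70 | 0.50 | ln(0.45/0.20) = 0.811 | 24 s | 57 s |
| 0.70 | 0.60 | ln(0.45/0.10) = 1.504 | 45 s | 105 s |

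The range is about 16–105 s, the first to fourth 30-s epoch. Wider assumptions (τ 30–80 s, AT 45–65%, start 20–30%, and a plateau equal to start + (1 − start) × load) give about 9–130 s.

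The time is proportional to τ. With P = 0.80 and AT = 0.55, ln(0.55/0.25) = 0.788. Then τ = 45 s gives 35 s and τ = 60 s gives 47 s. The apparent time to AT moves by 12 s although AT is identical.

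**3. Can an apparent AT arise with no threshold at all?**

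Take a model without a threshold, in fractions of peak, with VCO2 slower than VO2 (assumed):
- VO2 = 0.30 + 0.60 × (1 − exp(−t/τv))
- VCO2 = 0.25 + 0.60 × (1 − exp(−t/τc))
- Slope dVCO2/dVO2 = (τv/τc) × exp(t/τv − t/τc). It equals 1 at t = ln(τc/τv) / (1/τv − 1/τc).

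Results:
- τv/τc = 40/60 s: the slope starts at 0.67 and reaches 1 at 0.405/0.00833 = 49 s, with VO2 at 0.72.
- τv/τc = 50/80 s: the slope starts at 0.63 and reaches 1 at 0.470/0.0075 = 63 s, with VO2 at 0.73.

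A reading based on the VCO2–VO2 slope would call these points an AT, although the model contains none.

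**The case against.** The strongest reply is that the article gives no rule for reading AT, that such rules belong in an analysis plan or operating procedure, and that the comparison is already conditional ("In patients who reach anaerobic threshold (AT) in both positions") with an experienced assessor masked to position. Part of this stands. A reading rule could declare AT indeterminate, and masking limits reader bias. But no rule can supply a rising work rate, and masking does not help when the distortion lies in the signal.

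It is also fair that the kinetic values are assumptions and that the load is a percentage of a peak predicted from a COPD equation, which the Discussion itself calls a vulnerability. That uncertainty decides which of the two cases applies to a patient; it does not create a third.

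Four stronger readings are tempting, and the document does not support them:
- That the AT set is the plan's only view of anaerobic metabolism. The same section compares VO2 and VCO2 at isotime and plots VCO2 over VO2 and VE over VCO2.
- That the artefact is bound to differ between positions. Study rationale and purpose reports lower leg blood flow, lower muscle oxygen uptake and a lower anaerobic threshold when supine in healthy people, but says nothing about VO2 on-kinetics. A positional artefact is possible, not established.
- That 30-s averaging leaves only two or three possible values. The data are measured breath by breath, so epoch width is not the limiting problem.
- That the trial's main result is compromised. Stopping time does not depend on AT.

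**Conclusion.** The concern holds as a mismatch between the four AT-based secondary outcomes and the only test that could supply them. The mismatch follows from the protocol's stated load profile, the absence of an incremental test and the absence of listed lactate sampling, together with the standard meaning of a gas-exchange threshold. It does not depend on the kinetic figures. Those figures show only that, for a load above AT, the crossing falls in the initial transient and tracks the time constant. That values read as AT would mainly reflect VO2 and VCO2 kinetics is a physiological inference, not something the document states.

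The consequence is moderate: conditional secondary comparisons in a trial planned for 10 participants. The primary outcome and the planned isotime VO2 and VCO2 comparisons are unaffected.

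**What to change.** Remove time to AT, and VO2, VE/VCO2 and cardiac output at AT, from Secondary outcome measures. Keep VO2 and VCO2 at isotime as planned. Add VE/VCO2 and RER (VCO2/VO2) at isotime, and VO2, VCO2, VE/VCO2 and RER at end of exercise. If on-kinetics are of interest, add the VO2 mean response time from the breath-by-breath data and label it as kinetics.

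The cost is an amendment to the wording of the secondary outcomes. The added quantities come from VO2, VCO2 and VE, which the plan already uses, so no new measurement is needed. The downside is that the plan no longer reports a named AT comparison.

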### Recruitment and power

Given that HPS is a rare disease, and a majority of patients progress to either liver transplant or death relatively soon after diagnosis [10], recruitment to prospective trials in HPS has previously proven very challenging [30, 31]. Our recruitment will be further limited by the fact that only a subset of patients with HPS has orthodeoxia. Accordingly, we first estimated a recruitment target based on feasibility then set out to determine whether the demonstrable effect size with this sample would be both plausible and clinically meaningful. To estimate feasible recruitment, we searched the literature for studies describing the prevalence of orthodeoxia in cohorts of ≥ 10 HPS patients. However, we found only 4 small reports (14–20 patients each) reporting a highly variable prevalence of orthodeoxia, ranging from 14 to 88% of HPS participants (Table 3).

**Table 3 Tab3:** Characteristics of orthodeoxia in patients with hepatopulmonary syndrome

Author	Mean upright^†^ PaO_**2**_ (mmHg)	Prevalence of orthodeoxia^‡^, ***N*** (%)	Mean room air PaO_**2**_ in patients with orthodeoxia (mmHg) (SD)	Orthodeoxia (supine PaO_**2**_ − upright PaO_**2**_; mmHg)
Krowka et al., 1993 [32]	44.0	14/16 (87.5)	Upright: 44.0 ± 9 Supine: 62.0 ± 14	18.0
Martinez et al., 1999 [33]	65.2	2/5 (40.0)	Upright: 51.0 ± 3 Supine: 61.5 ± 2	10.5
Martinez et al., 2001 [34]	75.0	2/14 (14.3)	Upright: 63.5 ± 21 Supine: 71.5 ± 21	8.0
Gomez et al., 2004 [35]	69.0	5/20 (25.0)	Upright: 59.0 ± 6 Supine: 67.0 ± 5	8.0
Current study*	51.8	37/56 (66.1)	Upright: 48.1 ± 14 Supine: 61.9 ± 12	13.8

*Analysis performed in patients at the Toronto site of the Canadian HPS Database with a PaO_2_ < 80 mmHg, absence of significant concurrent lung disease contributing to hypoxemia, and absence of concurrent portopulmonary hypertension

^†^All studies defined “upright” as the sitting position, except for Krowka 1993 [32] and the current study, which defined it as the standing position

^‡^All studies defined orthodeoxia as a drop in partial pressure of arterial oxygen (PaO_2_) of greater than 5% or 4 mmHg in the upright compared to the supine position, except Martinez 1999 [33], which defined it as a drop in PaO_2_ greater than 10 mmHg in the upright compared to the supine position

We hypothesized that these variations in prevalence may have been due to the differences in covariates which predict orthodeoxia between study populations; however, the only study to attempt to explore predictors of orthodeoxia was that by Gomez and colleagues, in which the only significant predictors of orthodeoxia in a cohort of 20 patients with HPS were a lower baseline cardiac index and higher mean distribution of upright alveolar ventilation. Factors including baseline PaO_2_, etiology of liver disease, age, VO_2_, minute ventilation, and diffusion lung capacity of carbon monoxide (DLCO) were not significant predictors [35].

Given these limited sample sizes upon which to base our estimates, we performed an analysis of the prevalence and predictors of orthodeoxia in patients in the Canadian HPS Program Database. A priori, we identified the following candidate baseline predictors: age, sex, PaO_2_, MELD score, DLCO, macroaggregated albumin (MAA) shunt fraction, 6MWD, and presence of clubbing. We found that 37 out of 56 patients (66%) had orthodeoxia. In univariate analyses, lower baseline upright PaO_2_ and DLCO were significant predictors of orthodeoxia in HPS (Table 4).

**Table 4 Tab4:** Differences in baseline clinical characteristics between hepatopulmonary syndrome patients with and without orthodeoxia (current cohort)

Characteristic		No orthodeoxia	Orthodeoxia	***P*** value^†^
Age (years)	*N*	19	37	
	Mean ± *SD*	63.8 ± 11.9	60.4 ± 10.7	0.302
Sex—male	*N* (%)	8 (44.4)	22 (59.5)	0.294
MELD score	*N*	17	36	
	Mean ± *SD*	14.0 ± 3.8	12.4 ± 3.4	0.144
DLCO (% predicted)	*N*	18	35	
	Mean ± *SD*	64.0 ± 14.7	50.2 ± 14.7	0.005
MAA shunt fraction (%) [36]	*N*	10	30	
	Mean ± *SD*	17.2 ± 23.2	22.0 ± 13.8	0.551
Shunt fraction on 100% FiO_2_ (%) [37]	*N*	19	34	
	Mean ± *SD*	13.4 ± 6.0	14.6 ± 8.3	0.571
6MWD (m)	*N*	7	10	
	Mean ± *SD*	418.6 ± 109.2	441.8 ± 147.8	0.715
Clubbing	*N* (%)	12 (63.2)	22 (61.1)	0.882
PaO_2_ (upright) (mmHg)	*N*	19	37	
	Mean ± *SD*	59.0 ± 13.0	48.1 ± 14.3	0.006

*MELD* denotes model for end-stage liver disease score, *DLCO* diffusion lung capacity for carbon monoxide, *MAA* macroaggregated albumin, *FiO*_*2*_ fraction of inspired oxygen, *6MWD* 6-min walk distance, *PaO*_*2*_ partial pressure of arterial oxygen, *N* total number of participants, *SD* standard deviation

^†^Univariate analyses are presented for each variable, continuous variables assessed with a 2-sample *t*-test, and categorical variables with a chi-squared test. Variables were assessed on the same day as orthodeoxia or within an interval of ≤ 1 year

To our knowledge, this is by far the largest analysis of both the prevalence and risk factors for orthodeoxia in HPS. Given that patients with orthodeoxia had more severe hypoxemia, it was not surprising that our more “severe” HPS cohort (compared to other reports) had a high observed orthodeoxia prevalence of 66.1% (Table 3). We complimented this with an analysis of our current active HPS database, revealing that six patients currently meet the inclusion criteria. Additionally, a review of referrals in the last 3 years reveals that an average of 4 eligible patients is referred to our program each year. Based on a recruitment target of 50%, this analysis of the Canadian HPS Program Database suggests that we will be able to recruit 10 eligible participants to this study in the 4-year recruitment window allowed by study funding. We believe that this target is achievable, particularly with our pessimistic 50% recruitment target, since patients with HPS and orthodeoxia have no effective treatment options other than liver transplant, the study involves nearly no risk, and the study offers an opportunity to identify a clinically beneficial exercise strategy for the individual.

A crossover design has previously been successfully employed in patients with HPS [30]. The advantage of the crossover design in rare diseases such as HPS is that each participant will undergo both interventions, and within-person comparisons will limit confounding and reduce inter-subject variability, thereby reducing the sample size required to demonstrate an effect [38]. The crossover design is well-suited to an exercise intervention because there is no anticipated therapeutic carryover effect, obviating the need for a washout (we allowed for a 1-day minimum “washout” period for recovery from the prior exercise test). We established a 4-week maximum period between tests to minimize any possible period effect (i.e., to prevent significant disease progression by the time of the second test). The possibility of a period effect due to familiarity with the cycling exercise will be evaluated statistically.

Calculating the demonstrable effect size in this sample (10 participants) requires an estimate of the standard deviation of the expected change in stopping time between supine and upright positions. However, due to the novelty of this study design, there is no existing literature investigating supine exercise in patients with HPS. We also did not find any studies comparing supine and upright exercise in patients with cirrhosis without HPS. However, we did identify a study that employed a crossover design to evaluate the effect of hyperoxia (which has a similar physiologic impact to supine position in our cohort) on CWRET stopping time [39], in patients with interstitial lung disease—a condition in which the primary abnormality is a reduced diffusion capacity, which may have a comparable physiologic impact on exercise as the diffusion-perfusion defect of HPS. This study showed that exercise time increases significantly with hyperoxia compared to room air (21.9 ± 12.9 vs 11.6 ± 10.0 min, *P* < 0.001) [39], with a pooled standard deviation for change in exercise duration of 11.5 min. Applying this standard deviation, our crossover trial with a target sample size of 10 participants will be able to detect a difference of ≥ 2.85 min between the two interventions with power of 80% and a two-sided alpha of 0.05.

An increase in exercise time of 2.85 min is clinically meaningful in other hypoxemic diseases. In COPD, the minimal clinically important difference (MCID) for tLIM on CWRET is an increase of 33% or 105 s from baseline [26]. Bronchodilator trials suggest that clinical outcome improvements correspond to tLIM improvements of > 60 s [26]. Accordingly, an improvement of 2.85 min (171 s) would likely be clinically significant in our participants, who have more severe baseline exercise limitations than typical patients with COPD. With an estimated upright test duration of 3–8 min in our design [26], a change of 2.85 min would represent an improvement of between 36 and 95%, which again suggests a clinically meaningful improvement.

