### Participants

Participants will be sequentially recruited from the Canadian HPS Program Database between late 2019 and approximately mid-2023 (including a pause due to SARS-COV-2 for much of 2020). The eligibility criteria are outlined in Table 2. The drop-out criteria are provided under the “Exercise protocol” section.

**Table 2 Tab2:** Eligibility criteria

**Inclusion criteria** 1. Moderate HPS: (a) Liver disease (evidence of synthetic liver dysfunction and/or portal hypertension on biochemistry and/or imaging) (b) Moderate hypoxemia ▪ PaO_2_ < 80 mmHg ▪ AaDO_2_ ≥ 15 mmHg or ≥ 20 mmHg if age > 64 [1] (c) Intrapulmonary vascular dilatations (microbubbles seen in the left heart ≥ 3 cycles after the right heart on saline contrast echocardiography) 2. Presence of orthodeoxia (PaO_2_ decrease by > 4 mmHg when the patient moves from supine to upright position) **Exclusion criteria** 1. Pulmonary hypertension (a) Echocardiographic estimated right ventricular systolic pressure ≥ 50 mmHg (b) Right heart catheterization mean pulmonary artery pressure > 25 mmHg with pulmonary capillary wedge pressure ≤ 15 mmHg 2. Significant obstructive ventilatory impairment (FEV1/FVC ratio < 0.65) [14] 3. Known significant coronary artery disease 4. Significant neurologic, orthopedic, or rheumatological disorders preventing the use of a cycle ergometer 5. Other absolute contraindications to submaximal exercise testing [24] (a) Uncontrolled cardiac arrhythmia with hemodynamic compromise (b) Symptomatic severe aortic stenosis (c) Decompensated heart failure (d) Acute cardiopulmonary illness (e.g., venous thromboembolism, myocarditis, pericarditis, endocarditis, acute aortic dissection) 6. Moderate or severe ascites	

*PaO*_*2*_ partial pressure of arterial oxygen, *FEV1/FVC* forced expiratory volume in 1 s over forced vital capacity, *AaDO*_*2*_ alveolar-arterial oxygen gradient [PAO_2_ − PaO_2_, where PAO_2_ = [FiO_2_ (*P*_atm_ − *P*_H2O_) − PaCO_2_/0.8]], *AO*_*2*_ partial pressure of alveolar oxygen, *FIO*_*2*_ inspiratory oxygen fraction, *P*_*atm*_ atmosphere pressure, *P*_*H2O*_ water vapor partial pressure, *PaCO*_*2*_ arterial carbon dioxide pressure

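### The 80% power statement uses a recruitment forecast of 10 as the analysed number, with no allowance for losses and an unreconciled recruitment window, and its 2.85 min does not follow from the stated SD

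*Protocol article*

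**What the plan says.** All references are to the protocol article.

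- **Forecast (Recruitment and power).** Six patients are eligible now, about four eligible patients are referred each year, and half are expected to enrol. From this the authors conclude that "we will be able to recruit 10 eligible participants to this study in the 4-year recruitment window allowed by study funding".
- **Power (same section).** The text applies an SD of 11.5 min for the change in exercise time and states that "our crossover trial with a target sample size of 10 participants will be able to detect a difference" of at least 2.85 min "with power of 80% and a two-sided alpha of 0.05".
- **Dates (Participants; Trial status).** Recruitment runs "between late 2019 and approximately mid-2023 (including a pause due to SARS-COV-2 for much of 2020"). Trial status expects enrolment to finish around 1 July 2023.
- **Losses (Exercise protocol; Primary outcome measure).** "The dropout criteria for this study include unwillingness/inability to return for the second test", or an arrhythmic or hemodynamic stop on the first test. Separately, "We will exclude participants who stopped the exercise test due to either life-threatening arrhythmia or a drop in systolic blood pressure" from the primary analysis. No expected rate is given for any of these.

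**The concern.** The sample size was set by feasibility. The detectable difference at that size is then the argument that the trial is worth doing, because 2.85 min is presented as clinically meaningful. That argument needs the number of people who supply a within-person difference, not the number recruited. A participant with one usable test adds almost nothing to a supine-versus-upright comparison within person.

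The forecast also rests on four years of accrual, while the dates elsewhere are shorter and include a pause. If the analysed number is below 10, the stated power is too high even on the plan's own terms, and a non-significant result could be read as evidence against a 2.85 min effect that the trial had little chance of detecting.

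**Working it through.** **1. The plan's own figure.** Inputs from Recruitment and power: n = 10, SD of change 11.5 min, power 80%, two-sided alpha 0.05. For a paired or crossover comparison, detectable difference = k × SD / √n, where k comes from the noncentral t distribution.

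- Paired, 9 df: k = 3.150, so 3.150 × 11.5 / √10 = 11.45 min.
- Period-adjusted, 8 df: k = 3.201, so 11.64 min.
- Normal approximation: (1.960 + 0.842) × 11.5 / √10 = 10.19 min.

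The stated 2.85 min is not reproduced. A one-sided normal calculation gives 9.04 min. Treating 11.5 as a variance gives 3.0 to 3.4 min two-sided and 2.67 min one-sided. Working backwards by the t methods, 2.85 min at n = 10 needs an SD of the difference of 2.85 × √10 / 3.150 = 2.86 min (9 df) or 2.82 min (8 df). The normal approximation needs 3.22 min. None of these values is in the document.

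**2. Recruitment.** The rule implied by the text is recruits = 0.5 × (6 + 4 × years).

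| Years of accrual | Recruits | Basis |
|---|---|---|
| 4 | 11 | window in the forecast |
| 3.75 | 10.5 | late 2019 to mid-2023, pause ignored |
| 3.5 | 10 | same, later start |
| 3 | 9 | pause removed (length assumed) |
| 2.5 | 8 | longer pause removed (assumed) |

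The active 2.5 to 3 years assume that the pause lasted 0.75 to 1 year and that accrual during it is lost.

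**3. From recruited to analysed.** The document gives no loss rate. I assume 0 to 2 people lost or excluded. From 9 or 10 recruits this leaves 7 to 10, which I use as the working range. The worst corner, 8 recruits less 2, would be 6.

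**4. Consequences.** Ranges are from the paired (n − 1 df) and period-adjusted (n − 2 df) calculations. The middle columns accept 2.85 min at n = 10, with the back-solved SD of 2.82 to 2.86 min. The last two use the stated SD.

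| Analysed n | Power at 2.85 min, back-solved SD | Detectable difference, back-solved SD (min) | Power at 2.85 min, SD 11.5 | Detectable difference, SD 11.5 (min) |
|---|---|---|---|---|
| 10 | 80% | 2.85 | 11% | 11.5–11.6 |
| 9 | 74% | 3.1 | 10% | 12.3–12.5 |
| 8 | 67–68% | 3.3 | 9% | 13.3–13.7 |
| 7 | 58–60% | 3.6–3.7 | 8–9% | 14.6–15.3 |

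If the stated SD is right, 80% power at 2.85 min would need about 130 participants (paired t).

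**The case against.** A reader might infer that the plan's own rules yield only 7 to 9 analysed participants, and that this is why the trial lacks 80% power. The documents support neither step.

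On the number:
- The calendar span of 3.5 to 3.75 years still gives 10 to 10.5 recruits, and at four years the rule gives 11, one more than the target.
- The pause length is not stated.
- Recruitment is from a database of patients who have agreed to be approached, so people referred during the pause could be contacted later.
- The authors call 50% uptake pessimistic. With three active years (18 eligible), 10/18 = 56% uptake reaches 10.
- The two loss rules overlap, since a hemodynamic stop on the first test falls under both.
- The four years are those allowed by funding. Registration on 1 July 2019 to about July 2023 is four years, so the window may simply have been counted from then.

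On the cause, the drop from 80% to about 60% appears only with an SD of about 2.8 to 2.9 min, which the document never states. At the stated 11.5 min, going from 10 to 7 analysed costs about 2 percentage points.

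Most of this stands, and it limits the claim. It does not remove it. Late contact has limits: the article says most patients reach transplant or death fairly soon after diagnosis, and cites a median transplant wait of 200 days in severe disease, so some referrals during the pause could plausibly be lost. Reaching 10 recruits still does not give 10 analysed unless nobody is lost or excluded.

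**Conclusion.** The point holds in a limited form. The power statement equates recruited with analysed, although the protocol itself removes people from the primary comparison, and the four-year forecast is not reconciled with the stated dates and pause. The analysed number is uncertain. About 7 to 10 is plausible, conditional on the assumed pause, the fate of referrals during it, and 0 to 2 losses. It is not a figure the document yields.

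If 2.85 min at 10 is taken at face value, each lost participant costs roughly 6 to 9 points of power. That loss is secondary to the mismatch between 2.85 min and the SD of 11.5 min. At that SD the detectable difference with all 10 analysed is about 11.5 min, longer than the whole 3 to 8 min expected for the upright test. Correcting the SD alone would still leave a figure that rests on zero attrition and an unreconciled window, so both need attention.

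**What to change.** 1. Reconcile the recruitment window across Participants, Recruitment and power, and Trial status. Say how the pause, and patients referred during it, enter the forecast.
2. State the number expected to complete both tests and enter the primary analysis, with the assumed rates of non-return and of blood-pressure or arrhythmia stops.
3. In Recruitment and power, replace the single 2.85 min with the detectable difference for 7, 8, 9 and 10 analysed participants. Compute it from the stated 11.5 min, or from another SD of the within-person difference with its source and justification. Revise the argument about clinical meaning to match.
4. Interpret the primary result through its 95% confidence interval against the restated figure, so that a non-significant result is not taken as absence of effect.

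The cost is rewording and a recalculation. The published detectable difference becomes less favourable. No extra patients or procedures are needed.
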